## Abstract

**Background:**

Physical activity is a critical target for health interventions, but effective interventions remain elusive. A growing body of work suggests that interventions targeting affective attitudes toward physical activity may be more effective for sustaining activity long term than those that rely on cognitive constructs alone, such as goal setting and self-monitoring. Anticipated affective response in particular is a promising target for intervention.

**Objective:**

We will evaluate the efficacy of an SMS text messaging intervention that manipulates anticipated affective response to exercise to promote physical activity. We hypothesize that reminding users of a positive postexercise affective state before their planned exercise sessions will increase their calories burned during this exercise session. We will deploy 2 forms of affective SMS text messages to explore the design space: low-reflection messages written by participants for themselves and high-reflection prompts that require users to reflect and respond. We will also explore the effect of the intervention on affective attitudes toward exercise.

**Methods:**

A total of 120 individuals will be enrolled in a 9-week microrandomized trial testing affective messages that remind users about feeling good after exercise (40% probability), control reminders (30% probability), or no message (30% probability). Two types of affective SMS text messages will be deployed: one requiring a response and the other in a read-only format. Participants will write the read-only messages themselves to ensure that the messages accurately reflect the participants’ anticipated postexercise affective state. Affective attitudes toward exercise and intrinsic motivation for exercise will be measured at the beginning and end of the study. The weighted and centered least squares method will be used to analyze the effect of delivering the intervention versus not on calories burned over 4 hours around the time of the planned activity, measured by the Apple Watch. Secondary analyses will include the effect of the intervention on step count and active minutes, as well as an investigation of the effects of the intervention on affective attitudes toward exercise and intrinsic motivation for exercise. Participants will be interviewed to gain qualitative insights into intervention impact and acceptability.

**Results:**

Enrollment began in May 2023, with 57 participants enrolled at the end of July 2023. We anticipate enrolling 120 participants.

**Conclusions:**

This study will provide early evidence about the effect of a repeated manipulation of anticipated affective response to exercise. The use of 2 different types of messages will yield insight into optimal design strategies for improving affective attitudes toward exercise.

**Trial Registration:**

ClinicalTrials.gov NCT05582369; https://classic.clinicaltrials.gov/ct2/show/NCT05582369

**International Registered Report Identifier (IRRID):**

PRR1-10.2196/46560

## Introduction

### Background

Exercising is crucial for maintaining and improving health and fitness and is linked to improvements in both physical and mental health [1,2]. However, only 53% of Americans [3] meet the recommended threshold of 150 active minutes a week [4], and only 23% meet guidelines for both muscle strengthening and aerobic exercise [3], creating a critical need for effective interventions to help Americans exercise. Health researchers have explored ways to leverage technologies such as smartphones and wearables to meet this need, devising interventions that use displays, messages, and other technological channels to encourage physical activity [5]. Reviews of this extensive body of work have found that mobile interventions hold promise [6,7], with a correlation between engagement with the mobile health (mHealth) intervention and efficacy [7]. However, the effects of mHealth interventions on physical activity thus far have often been relatively modest [5,8], when they are effective at all [9,10]. In addition, effects generally do not last long term [11].

Most existing mHealth interventions use a limited set of strategies to encourage physical activity [12,13]. In particular, many interventions rely on goals- and self-efficacy–related strategies, such as supporting goal setting and self-monitoring, providing feedback on performance [5,8], offering rewards [14], and providing some form of social support [8]. However, this range of approaches is relatively narrow compared with a full taxonomy of behavior change techniques [15]. One review found that only 39 out of 93 techniques were used across all top physical activity mobile apps [12]. One potential avenue for improving the efficacy of physical activity mHealth interventions is to devise interventions that expand the range of the targeted mechanisms of behavior change, for example, by developing affective interventions.

### The Potential of Affective Interventions for Physical Activity

Interventions that specifically target affect (eg, by using emotion-related behavior change techniques [16]) have the potential to improve the performance of behavior change mHealth apps. Affect is a challenging target for behavior change apps, in part because the relationship between exercise and affect is not straightforward. First, researchers have described a wide variety of separate constructs related to affect [17], including how an individual feels in the moment (incidental affect), their conscious or unconscious assessments of the pleasantness of exercise (affective attitudes and affective associations, respectively), how an individual feels as a result of performing target behavior (affective response), and other aspects of emotional experience [17,18]. Different models of behavior change link these individual constructs differently to health behavior (eg, by listing affect as a component of more general attitudes that factor into behavioral intention [19] or as individual constructs that affect motivation through a variety of conscious and nonconscious processes [17,20-24]). Second, the effect of exercise on individual affective constructs itself varies greatly; for instance, the intensity of exercise has been shown to have an impact on incidental affect during exercise: gentle physical activity is associated with more positive affect, and vigorous exercise is generally associated with a negative affective shift [25].

Despite these complexities, affective constructs are a promising target for intervention. A growing body of work is demonstrating that affective constructs are meaningful predictors of exercise behavior [21]; for instance, positive nonconscious affective evaluations of exercise are associated with higher exercise volume [21] and play a role in both conscious and nonconscious processes regarding exercise behavior [26]. The effect of differences in affective attitudes to exercise can be powerful: 1 study found a 38-minute weekly increase in exercise for every increase of 1 unit on the Feeling Scale (a scale used to measure affective valence [27]) at the 6-month mark of an aerobic exercise program and a 41-minute increase at 12 months [28]. Affective assessments of exercise are even more impactful than other determinants such as self-efficacy [21,29], and 1 study found that sending affectively framed messages yielded more exercise behavior than cognitively framed messages [30].

One affective construct that holds potential for influencing physical activity is *anticipated affective response*, or how an individual expects that a target behavior will make them feel [17]. Generally, affect takes a negative shift during vigorous exercise but rebounds immediately afterward [25]. Much evidence has associated exercise with positive affective states or, at minimum, recovered affective states afterward, starting immediately after exercise and lasting for as long as a day afterward [25,31]. Although the evidence concerning the relationship of positive postexercise affect with exercise intention is somewhat mixed, and there is need for more research on affective responses to exercise to understand individual variation and guard against biased results [32,33], there is some evidence that positive postexercise affect influences affective attitudes toward exercise [34], which themselves are linked to improved exercise behavior [21,34]. Moreover, *anticipated* positive affective response has been positively associated with exercise intention [35] and behavior [17,18], and *priming* people to expect to feel good after exercise has been shown to increase positive affect over the course of exercise [36], postexercise affect [35,36], and exercise intention [35]. The manipulations thus far of anticipated positive postexercise affect have not consistently resulted in increased exercise behavior [35,36], but priming interventions that trigger increased mental elaboration have been associated with more positive postexercise affect [35], suggesting that how a priming intervention is designed may influence its effectiveness. This finding echoes the findings in human-computer interaction literature that reflection at key stages can affect physical activity behavior [37] and suggests that work is needed to understand what forms of interventions can be most effective.

### Text Messaging Physical Activity Interventions

One relatively common form of intervention is SMS text messaging. With >95% of American adults owning a mobile phone capable of sending and receiving SMS text messages [38], SMS text messaging interventions are broadly accessible and can reach more populations than interventions that rely on smartphones [39]. SMS text messages may make up stand-alone interventions or act as components in a larger intervention [39]. Reviews of SMS text messaging interventions for physical activity have encouragingly found positive effects in reducing weight and promoting physical activity [39,40], although evidence is more ambiguous for specific populations [39,41]. Importantly, the efficacy of SMS text messaging interventions rests in part on their content [30] and tailoring, as well as other characteristics [39].

### Study Contribution

In this study, we will conduct a microrandomized trial [42] (trial registration: ClinicalTrials.gov NCT05582369) to evaluate the effect of a stand-alone SMS text messaging intervention designed to manipulate anticipated postexercise affect to increase exercise behavior. Microrandomization is an efficient trial design that enables causal inference with relatively small samples [42,43]. The primary objective is to determine whether manipulating postexercise affect before planned exercise increases calories burned over the 4-hour period when individuals planned to exercise. Our study extends prior research by examining the influence of anticipated postexercise affect not only on exercise intentions but also on actual exercise behavior. The study will contribute empirical findings on the effect of manipulating anticipated postexercise affect on exercise duration and intensity, actual postexercise affect, and other measures of affective attitudes toward exercise, as well as qualitative findings about how such interventions should be designed.

## Methods

We will conduct a 9-week microrandomized trial of an SMS text messaging intervention to make the affective rewards of exercise salient before planned exercise, recruiting adults from the general American population who have an Apple Watch and an iPhone. The field deployment will be followed by interviews to learn about participant experiences with the intervention.

### Intervention Description

The intervention consists of SMS text messages about feeling good *after* exercise, which are sent to participants *before* they exercise to manipulate anticipated postexercise affect. There are 2 types of affective intervention messages: high-reflection messages and low-reflection messages (Table 1). High-reflection prompts ask participants to think about and write down, in the reply message, topics related to feeling good after exercise. Low-reflection SMS text messages do not require a response. They contain messages that participants will write themselves at the time of study enrollment, using fill-in-the-blank templates. The research team will review these messages at the time of enrollment to ensure that they are topical. The fill-in-the-blank templates were developed through a series of pilots on Amazon’s Mechanical Turk, a website that enables paid crowdworkers to complete web-based tasks. The final set consistently generated topical responses from Mechanical Turk respondents. Out of 18 messages (n=9, 50% high-reflection prompts and n=9, 50% low-reflection prompts, enough for participants to complete the study without repeated messages), participants will receive a randomized subset. Having 2 types of SMS text messages will both generate variety for participants and allow us to explore differences in participant experience resulting from different interaction mechanisms; although both are highly personalized, high-reflection messages provoke reflection and mental elaboration in the moment. In other works, mental elaboration or reflection in written form at different planning or pre-exercise stages has been associated with improved postexercise affect [35] and increased step counts [37].

**Table 1 table1:** Primary intervention message types and examples.

Message type	Participant involvement	Example messages
High-reflection messages	Researcher generated; participant response via texting required	What’s your favorite thing about the way exercise makes you feel afterwards? What positive feelings do you want to experience after exercise today? Name three. When was the last time you did some exercise outside? Tell us what it was and one good feeling you felt afterwards.
Low-reflection messages (templates)	Participant generated based on researcher-created fill-in-the-blank templates; no response required	Exercise can be its own reward, because ______ makes you feel _____ afterwards. (Fill in the first blank with something you enjoy about exercise. Fill in the second blank with a good feeling that you get from exercise) Working your body makes you feel _____ after you exercise. (Fill in the blank with a good feeling you get from exercise) Exercise makes you feel _____ afterwards, because ____. (Fill in the first blank with a good feeling that you get from exercise. Fill in the second blank with a reason exercise makes you feel good)

### Study Procedures

#### Microrandomized Trial

To investigate the effect of the intervention, we will conduct a 9-week microrandomized trial. Participants will complete self-report assessments at enrollment and at the study close. During the 9-week deployment, participants will be randomized twice a week, before planned exercise sessions, to receive an affective intervention message (40% probability), a simple reminder message (30% probability), or no message (30% probability). The study design and measurement points are illustrated in Figure 1 and Table 2. Instruments are listed by study phase in Textbox 1, and specific measures are detailed in Table 3.

**Figure 1 figure1:**
[figure not shown]
Randomization procedure.

**Table 2 table2:** Participant activities and measures by study phase.

Study phase	Participant activities	Measures
Enrollment	Complete low-reflection prompt	Affective Measures SRQ-E^a^ PACES-8^b^
Trial period: 9 wk^c^	Plan 2 exercise sessions/wk Receive and read study SMS text messages Respond to high-reflection prompts via texting Wear Apple Watch Report exercise afterward	Planning Questionnaire Exercise Self-Report Questionnaire
Study close	Closing Questionnaire	Affective Measures SRQ-E PACES-8
Optional interviews	Answer questions about experience with the intervention	N/A^d^

^a^SRQ-E: Exercise Self-Regulation Questionnaire.

^b^PACES-8: Physical Activity Enjoyment Scale.

^c^Affective intervention messages: 40% probability, reminder messages: 30% probability, and no message: 30% probability.

^d^N/A: not applicable.

Measures used by study phase.
**Enrollment**
Consent and enrollment questionnaire (contains affective items)Exercise Self-Regulation Questionnaire (SRQ-E)Physical Activity Enjoyment Scale (PACES-8)
**Microrandomized trial (9 wk)**
Planning questionnaire (a version with a question about anticipated postexercise affective state for the next exercise session included will be sent once halfway through study)Exercise self-report questionnaireSensor data collection
**Exit**
Closing questionnaire (contains affective items)SRQ-EPACES-8

**Table 3 table3:** Specific measures used in the study.

Specific measure or topic; number of times measured during the study		Questionnaires	Items; answer options
**Pre- and postintervention measures**			
	SRQ-E^a^ [44,45]; 2	Consent and enrollment, closing	Refer to the SRQ-E [44]
	PACES-8^b^ [46]; 2	Consent and enrollment, closing	Refer to the PACES-8 [46]
	Baseline activity (self-report); 1	Consent and enrollment	How many days a week do you typically exercise? By exercise, we mean moderate or intense physical activity that lasts for at least 20 minutes (e.g. a brisk 20 minute walk, yoga, running, swimming, etc.); 1 to ≥6
	General affective attitude; 2	Consent and enrollment, closing	How much do you like or dislike exercising?; 7-point scale ranging from I hate exercising to I love exercising
	Affective association; 2	Consent and enrollment, closing	When considering exercise, I feel...; 7-point scale ranging from sad to happy
	Anticipated regret (adapted from the study by Conner et al [47]); 2	Consent and enrollment, closing	If I were not to exercise this week, I would regret it; 7-point scale ranging from very unlikely to very likely
	Anticipated pride (adapted from the study by Conner et al [47]); 2	Consent and enrollment, closing	If I were to exercise this week, I would feel better; 7-point scale ranging from very unlikely to very likely
	General during-exercise affect; 2	Consent and enrollment, closing	While you are doing exercise, how do you typically feel?; free text Rate how good or bad you typically feel while you are doing exercise; Feeling Scale [27]
	General postexercise affect; 2	Consent and enrollment, closing	After you finish exercising, how do you typically feel?; free text Rate how good or bad you typically feel after exercising; Feeling Scale [27]

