### Participants

US residents with an iPhone and Apple Watch who are aged at least 18 years and have not been medically advised against physical activity are eligible to participate. Participants will be recruited through web-based channels such as email lists and relevant internet forums. They will be informed about the study and will give consent through a web-based questionnaire.

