### Data Analyses

#### Primary Analysis

Our primary interest is the average effect of the affective message intervention across time on calories burned during the planned exercise periods compared with no message being sent. To assess this effect, we will use the centered and weighted least squares method, a standard approach for analyzing microrandomized trial data that allows for robust causal inferences about treatment effects [53] and accounts for correlations in longitudinal data by nesting outcomes within participants. The covariates in our analysis will include time in study, the prior week’s proximal outcome, self-reported baseline activity levels, age, and gender.

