#### Secondary and Exploratory Analyses

Additional analyses of the microrandomized trial data will investigate the time trend of the effect of affective messages (ie, the change in the effect of the affective messages over the duration of the study), the contrast between affective messages and reminder messages, and separate over-time and time-trend effects of low-reflection and high-reflection messages. In addition, we will investigate the intervention’s effect on other outcomes, such as step count and active minutes for the 4-hour planned exercise interval, as collected from the participants’ Apple Watches. These analyses, as in the case of the primary analysis, will all be conducted using the centered and weighted least squares method.

In addition to the microrandomized trial analyses, we will conduct a number of exploratory analyses of the affective measure data. We will examine potential changes in the anticipated postexercise affect by investigating changes in pre- and postintervention ratings on the Feeling Scale [27]. Exploratory analyses will include an investigation of changes in other affective measures used and the role of potential moderating factors such as baseline activity level, planned exercise intensity, and exercise intensity on postexercise affective state predictions. In addition to these quantitative analyses, we will thematically analyze interview data in accordance with the principles described in the study by Braun and Clarke [54]. After transcribing the interviews, we will use an iterative inductive approach to explore themes in the data around participants’ underlying needs and the impact the intervention had on their lives. We will triangulate interview responses with observed participant behavior and responses to the closing questionnaire to get a full picture of participant experience with the intervention and insight into appropriate outcome metrics for future iterations.

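### The baseline activity item has no answer for 0 days a week although no minimum activity is required; this blurs an exploratory moderator and the sample description, but not the primary effect

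*Protocol article*

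**What the plan says.** Table 3, in the block of pre- and postintervention measures, lists one baseline activity item, asked once in the enrollment questionnaire: "How many days a week do you typically exercise". It defines the term: "By exercise, we mean moderate or intense physical activity that lasts for at least 20 minutes". The examples and answer range follow: "e.g. a brisk 20 minute walk, yoga, running, swimming, etc.); 1 to ≥6". No answer for 0 or none is listed.

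The opening of Methods describes "recruiting adults from the general American population who have an Apple Watch and an iPhone". The Participants section requires US residence, the two devices and an age of at least 18 years, and says that people who "have not been medically advised against physical activity are eligible to participate". Neither place sets a minimum activity level. Informed Consent and Participation mentions an eligibility screener but states no activity criterion.

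The variable is then used in these places:

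- Primary Analysis lists among its covariates "self-reported baseline activity levels, age, and gender".
- Secondary and Exploratory Analyses will look at "potential moderating factors such as baseline activity level", with planned and actual exercise intensity. The outcome there is participants' predictions of how they will feel after exercise.
- Study Procedures Overview plans to stratify the interview sample on characteristics that include exercise frequency. It does not say which item supplies that frequency.

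**The concern.** The answer range and the eligibility rule do not fit together. An eligible adult who does no 20-minute session of moderate exercise in a typical week has no truthful answer. That person may choose 1 or, if the form allows it, leave the item blank. In both cases 0 and 1 day a week cannot be told apart, and no later item in Table 3 asks again about typical activity before the study.

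At stake is the low end of the activity scale. The Introduction motivates the trial by how many Americans exercise too little, so readers will want to know how many participants were inactive at entry. The exploratory moderator analysis also needs that end of the scale.

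**Working it through.** **1. The plan's own figure.** The article gives no figure that depends on this item. Its sample size of 89 was reproduced to confirm that. The check used a noncentral F test with 1 numerator degree of freedom, 18 decision points, availability 0.7, effect 0.2, significance .05 and power 0.9. The noncentrality is N × 18 × 0.7 × p(1 − p) × 0.2². With p = 0.4 and N = 89 this is 89 × 18 × 0.7 × 0.24 × 0.04 = 10.8, and 89 is the smallest N that reaches the power. Baseline activity does not enter the formula.

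**2. Effect on the primary estimate.** A simulation used 89 participants, 18 decision points, a 70% chance that a decision point enters the contrast, and a probability of 4/7 for the affective message within it (0.4 / 0.7). The true effect was 0.2 and the model used a centered treatment with participant-clustered standard errors. These inputs were assumed: the true share at 0, an even spread of the rest over 1 to 6 days, and an outcome that rises by 0.15 per day. There were 400 runs per row. Baseline activity was the only covariate.

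| True share at 0 | Estimate (SE), true coding | Estimate (SE), 0 scored as 1 |
|---|---|---|
| 5% | 0.1990 (0.0591) | 0.1990 (0.0591) |
| 10% | 0.1985 (0.0589) | 0.1984 (0.0589) |
| 20% | 0.2016 (0.0593) | 0.2016 (0.0593) |
| 30% | 0.1983 (0.0590) | 0.1981 (0.0592) |

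The coding makes no material difference. Treatment is randomized at each decision point independently of the covariate, which serves only precision. The simulation covers a 0 recorded as 1, not a blank answer.

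**3. Effect on the baseline variable.** Let z be the true share at 0. Assume the others split .10/.20/.25/.20/.15/.10 over 1 to 6 days (mean 3.4, mean square 13.7). The article supports neither assumption. Write T for true days and R = max(T, 1) for recorded days.

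- Share of recorded 1s that are really 0: z / (z + 0.10(1 − z)).
- Ratio by which a slope that is linear in T is inflated when R is used: cov(T, R) / var(R).

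Worked for z = 0.10:

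- Share: 0.10 / (0.10 + 0.09) = 53%.
- Means: R is 0.10 + 0.9 × 3.4 = 3.16, and T is 3.06.
- cov = 0.9 × 13.7 − 3.06 × 3.16 = 2.66.
- var(R) = 0.10 + 0.9 × 13.7 − 3.16² = 2.44.
- Ratio: 1.09.

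| z | Recorded 1s that are 0 | Slope ratio | Correlation of R with T |
|---|---|---|---|
| 1% | 9% | 1.01 | not computed |
| 2% | 17% | 1.02 | not computed |
| 5% | 34% | 1.05 | .992 |
| 10% | 53% | 1.09 | .988 |
| 20% | 71% | 1.15 | .985 |

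So the lowest category can be badly mixed while the variable as a whole still ranks people almost correctly.

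**The case against.** The strongest reply is that few participants may be at 0. They own an Apple Watch, come through web channels that include relevant internet forums, and are asked to plan two sessions of at least 20 minutes each week for 9 weeks. The screener's items are not shown either. This stands as far as size goes: at 1% or 2% the distortion is trivial. It does not remove the mismatch, because the item asks about typical behavior at enrollment, whereas planning is what participants intend during the study. An inactive adult who wants to start is eligible.

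Three stronger readings are tempting, and the article supports none of them.

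- A reader might infer that the plan loses its test of whether the message works in inactive people. No such test is planned. The named moderation concerns affect predictions, and the message-effect analyses listed do not include moderation by baseline activity.
- A reader might infer that blank answers would remove participants from the primary model. The article does not say whether the item can be skipped, and it does not call for complete-case analysis. The Missingness section covers questionnaire data in general terms.
- A reader might infer that the primary effect is biased because one of its covariates is mismeasured. The simulation shows otherwise.

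Watch data and reports of unplanned exercise do show activity during the study, but not typical activity before it.

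**Conclusion.** The mismatch is real and minor. As printed, the only baseline activity item cannot record an eligible adult who exercises on 0 days a week. The primary treatment effect and the sample size are essentially untouched.

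The harm is limited to the exploratory moderation of affect predictions by baseline activity, the description of the sample and, if this item is the source, the exercise-frequency strata for interviews. With 1% to 20% at 0, a linear moderator slope would be overstated by about 1% to 15%, and 9% to 71% of recorded 1s would be 0s. These ranges rest on an assumed activity distribution, on everyone at 0 answering 1, and, for the slope, on exact linearity. The Introduction's figure that 53% of Americans reach 150 active minutes a week does not give the share at 0.

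**What to change.** - Add a 0 option to the enrollment item for participants still to be enrolled. With 57 of 120 enrolled by the end of July 2023, that is up to 63 people. If the fielded form already offers 0, correct Table 3 instead.
- Label and code the lowest category as 0–1 for everyone in the primary model and in the main moderator analysis, so that early and late enrollees are treated alike.
- Use a separate 0 level only in a sensitivity analysis restricted to those who answered the corrected item at enrollment. It will be thin: 5% to 20% of 63 is about 3 to 13 people.
- If earlier enrollees who answered 1 or left the item blank are asked a follow-up question, use the answers for description only. They would be given after exposure to weekly planning and the messages, so they should not serve as a baseline moderator.

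The cost is one answer option, a relabeled category and, optionally, one short text message. The downside is that 0 and 1 stay pooled for those already enrolled. The main moderator slope therefore keeps whatever distortion the pooling causes, and this should be stated when it is reported.
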